## Abstract

**Background:**

Given the emotional demanding nature of social services, we developed a brief daily body-mind-spirit (BMS) program and successfully piloted it with workers at elderly services. The proposed study focuses on community mental health workers who are often under chronic stress and vulnerable to burnout.

**Methods:**

The study aims to evaluate the program for fostering sustainable emotional capacity and work engagement for community mental health workers. A multi-site randomized controlled trial design is adopted. All the 24 the Integrated Community Centre for Mental Wellness (ICCMW of Hong Kong will be approached to join this program. Assuming conservatively, 60% ICCWM (14 centers) will respond and participate. At each site, a pair of intervention and control groups will be run. The targeted total sample size is 224. To investigate the course of changes in burnout and engagement, each group will last 6 months, including 3-month intervention and 3-month follow-up. Measures will be taken at monthly intervals.

**Discussion:**

In light of literature and the pilot trial’s findings, participants in the Brief Daily BMS intervention group are expected to have a reduced burnout level and a narrowing of range in work engagement during the 3 months intervention. And within the 3 months post-intervention period, a rebound of burnout level and a widening of range in work engagement are expected to be observed in the same group of participants. Hopefully, this study will contribute to the deeper understanding of burnout and work engagement, and shed light on sustainable intervention for emotionally demanding workplaces.

**Clinical Trial Registration:**

The trial has been registered in the Clinical Trials Centre of the University of Hong Kong. HKUCTR-2763 Registered 27 December 2019 – Retrospectively registered, http://www.hkuctr.com/Study/Show/eb930d24e2c647afb7a922055163f24b.

## Background

### Community Mental Health Workers in Need of Continued Emotional Support

Work burnout is identified with three elements: cynicism, exhaustion and reduced efficacy (Maslach et al., 2001). Burnout is common in all sectors - governmental, commercial and non-governmental organizations. In positions where job demands/resources matching is strained, employees often experience chronic stress and are vulnerable to burnout (Schaufeli and Bakker, 2004). Prolonged intense work stress is associated with health and mental health problems (Sanderson and Andrews, 2006). At an organizational level, productivity and quality suffer (Lerner et al., 2004). There are more sick leaves, work injuries and staff turnover. The continued trend of globalization and advance in information technology has intensified competition and threatened job security in many industries. The relentless demands for productivity and quality enhancement are both real strains and psychological stresses for workers.

The welfare sector is no exception and staff well-being at workplace is a concern. Two common characteristics of human services work, intensive emotional involvement and humanitarian values, would function as vulnerable factors. Social workers who experienced the overwhelming emotional involvement, as a form of emotional labor, will be exposed to emotional exhaustion, which is a key characteristic of work burnout (Maslach et al., 2001). Also, it is common to have discrepancies between one’s personal/professional values and the reality of work, which may induce intense psychological conflicts. For some workers, a coping mechanism would be a disengagement from work (Park and Folkman, 1997). Moreover, an individuals’ apathetic attitude can affect co-workers as well as the morale of a work team (Schaufeli and Bakker, 2004).

In the context of Hong Kong, the extreme work-life imbalance is common and adds to the stress of workers (Ng et al., 2009b, p. 179). In many work teams, overtime work is a norm rather than the exception, and members are under pressure to conform at the cost of sacrificing some personal and family time. In the welfare sector, additional stresses include relentless pressure on securing funding, fulfilling elaborative documentation procedures, meeting the increasing expectations of service users, and in some cases, dealing with unfriendly resistance from local residents. There is a widespread feeling among social service workers in Hong Kong that job burnout has become an epidemic (Ng, 2008). A worrying indicator is persistently high staff turnover, with double-digit annual staff turnover rate being a norm.

The proposed study focuses on the well-being of community mental health workers. In 2010 the Social Welfare Department, Hong Kong SAR government restructured the fragmentized community mental health services around a new mega, one-stop service named ICCMW (Ng, 2015, p. 8). The scope of service of ICCMW is extremely wide, ranging from education and prevention to treatment and rehabilitation. Targeted service users include people suffering from SMI and common mental disorders, as well as healthy people in the community. Operational modes include rapid response to psychiatric emergency, time-limited casework, long-term support for people with chronic SMI, day center and community development. As a result of the service restructure, a total of 24 ICCMWs were established covering the whole territory of Hong Kong, which has a population of over 7 million. The 24 ICCMWs are manned by a totally of about 700 mental health workers. Most of them have a background in social work, nursing and occupational therapy. Charged with such a wide scope of responsibility, ICCMWs are overstretched to achieve all the goals and pledged service outputs (Ng, 2015, p. 36). Moreover, due to the nature of work, community mental health workers often spend much time in performing home visit on their own. This makes it difficult to create a supportive teamwork environment. As a result of all these factors, community mental health workers are under chronic stress and are vulnerable to burnout. They need continued support for sustainable emotional capacity and work engagement.

### A Paradigm Shift: From Symptoms-Reduction to Fostering Positive Well-Being

In social services, human capital is the most important asset of the organization. It is critically important to sustain and foster the staff’s well-being. Regarding interventions, there are practical limits concerning what may be done at the organizational level due to the operational constraints, such as contracts with the funding bodies and expectations of service users. Nevertheless, previous studies have suggested that while the tangible incentives are meaningful, they are not the paramount factors to influence the engagement and work burnout (Schaufeli and Bakker, 2004).

At individual levels, existing studies mainly concentrate on the symptoms reduction and have only shown quite limited short-term effects (Schaufeli and Bakker, 2001; Richardson and Rothstein, 2008; Goldgruber and Ahrens, 2010). Moreover, a symptoms-reduction mode would over-simplify work stress as negative, which is conceptually wrong and unhelpful. Some workers may see the ‘symptoms’ as evidence for requesting more tangible benefits from the employers. The purpose of instilling ownership of one’s personal well-being is defeated.

Our studies in Hong Kong have demonstrated the effects of holistic care culture in alleviating burnout and promoting work engagement (Ng et al., 2011; Fong et al., 2016). The updated researches about well-being in the workplace tend to treat work engagement as an outcome measure. In opposition to burnout, work engagement characterized as three components: passion, vigor, and absorption at work of employees (Schaufeli and Bakker, 2004; Fong and Ng, 2012; Ng, 2014). While appearing to be opposite concepts, work engagement and burnout have been revealed to be rather independent, demonstrating negative correlation at only mild to moderate magnitude (Schaufeli and Bakker, 2004; Gonzalez-Roma et al., 2006; Ng et al., 2011). Otherwise speaking, lack of burnout and existence of engagement may not necessarily happen at the same time. Because burnout and engagement influence well-being independently (Hakanen and Schaufeli, 2012), both of them need to be addressed.

A new tendency is adopting a positive-oriented approach to enhance workplace well-being (Gonzalez-Roma et al., 2006; Ng et al., 2011; Fong et al., 2016). One of these positive approaches is to foster daily spiritual experience, which showed encouraging possibilities (Holland and Neimeyer, 2005). Daily spiritual experience can be understood as the interaction between a person’s daily behavior/emotion and the transcendence in ordinary life (Underwood, 2006; Ng et al., 2009a). For instance, feeling blessed by a higher power, finding peace and strength deep inside, and experiencing intimate transpersonal connections. Previous studies show that a sound correlation existed between daily spiritual experience and well-being (Ellison and Fan, 2008).

Because of the tight association among BMS, holistic care should include all the three elements in fostering well-being (Ng and Chan, 2005, p. 71). In practice, the usual starting point is to link with the body (Ng, 2009, p. 128). Building the connection with their own body increases people’s awareness and helps to ground the self in the present moment. Being more grounded, people may broaden their awareness and build a connection with the mind and spirit. Brief BMS practices have been evaluated and assessed with plenty of evidences in a wide range of clients, for instance, people with mood and sleep disturbances, chronic fatigue, and survivors of critical incidents (Ng et al., 2006; Chan et al., 2016, 2017; Ji et al., 2017). Given the emotional demanding nature of social services, we developed a brief daily BMS program and successfully piloted it with both professional and care workers at elderly service (Ng, 2014). The proposed study aims to further and more rigorously evaluate the efficacy of the program.

### What We Have Done: Piloted a Feasible Brief Daily Body-Mind-Spirit (BMS) Program and Validated Scales Essential for Pursuing Rigorous Trials

#### The Brief Daily Body-Mind-Spirit Program for Social Service Workers

It is challenging to develop a brief daily BMS program that is feasible for busy social service workers of varied cultural and educational backgrounds. The program should pay attention and respect to religious pluralism, including not only one single religion, as well as spiritual, but non-religious orientation or practice. Finally yet importantly, this intervention should be concise otherwise it would become a burden for the practitioners, including facilitators.

Taking into consideration the above mentioned, we cooperated with a major elderly community center in Hong Kong and applied a brief daily wellness program providing 15 min BMS practice for their staff in a format of small group on every workday. The targeted group size is around 8–12. We trained a social worker of this center as the group’s facilitator. The group sessions are delivered in a compact and quiet room within their center. Sitting on the floor with a yoga mat created a relaxing environment for the group members. For those who are difficult to sit on the ground, chairs were provided. Each session runs about 15 min and will contain three standardized sections: Cooling down, Proverb sharing and Energy activity. The contents of the intervention will be described in the method section of this manuscript.

We have piloted this brief daily BMS program separately for professional and care workers at elderly services for a duration of 1 month (Ng, 2014). Both qualitative and quantitative findings supported the acceptability and feasibility of the intervention, and its potential efficacy in reducing burnout and fostering sustainable emotional capacity and work engagement. Attendance rate in both groups exceeded 80%. More encouragingly, the dropout rate was zero in both groups. In subsequent focus group meetings, participants shared that they felt revitalized with positive energy after every meeting, and thus could better work with service users at workplace and enjoy the time with family members in the evening. Both the facilitators and participants enjoyed participating in the program and did not see it as an additional burden. Some participants expressed that they actually looked forward to it on every workday during the pilot period, and wished that the program could be continuously offered at their workplace.

The quantitative findings of the pilot trials are also encouraging. Despite a small sample size (totally *N* = 16), reduction in burnout was significant in both groups. Effect size was in the range of moderate magnitude. However, the positive changes at 1 month after completion of the program appeared to diminish. This suggests that a continued or a longer duration program is desirable.

Findings of change in work engagement go beyond the expectation, but perhaps are most inspiring. In the group with a high baseline engagement level (4.0 out of a theoretical range of 0–6; *SD* = 0.8), a significant reduction in engagement was observed, in parallel to a mark reduction in burnout. In the group with an average baseline engagement level (3.0; *SD* = 1.0), no significant change in engagement level was observed, but in parallel, there was also a mark reduction in burnout.

A tenable theory is that a higher work engagement level is not always desirable. Several studies indicate the “dark side” of “over-engagement”: extremely high level of work engagement can be counterproductive to individual well-being and organizational performance (Bakker et al., 2011). For example, over-engagement may lead to workaholics, unbalance between work and life, and harm to interpersonal relationships (Beckers et al., 2004; Beal et al., 2005). Furthermore, it is also unrealistic to expect that employees are kept “engaged” all the time. Bakker et al. (2011) argues that perhaps a fluctuating level of work engagement is desirable.

The finding of our trial and previous literature shed the light on the understanding of work engagement: an optimal range of engagement level may exist. A good analogy is that in an endurance race, the one who presses him/herself too hard will sooner or later drop out of the race. Perhaps engagement is like a ‘fire’ in our heart fueling us at the workplace. However, if the ‘fire’ is overly strong, it will ‘burn’ us. The findings from our pilot trials seem to suggest that the appropriate intervention goal with work engagement is to facilitate participants finding an optimal, sustainable level. Neither too low nor too high is desirable.

#### Chinese Utrecht Work Engagement Scale (C-UWES)

The original Utrecht Work Engagement Scale (UWES) has 17 items covering 3 domains, namely Dedication, Absorption, and Vigor (Schaufeli et al., 2002). We validated this scale with 992 workers in more than 30 Hong Kong elderly service centers. After careful exploratory and confirmatory factor analysis, we removed the unsatisfactory items and produced a 9-item solution consisting of the same 3 domains of Vigor, Dedication and Absorption (Fong and Ng, 2012). Cronbach’s alpha coefficients of this shortened scale were 0.88 for the whole scale, and 0.70 to 0.77 for the 3 subscales.

#### Chinese Daily Spiritual Experience Scale (C-DSES)

Daily spiritual experience (DSE) refers to a person’s perception of involvement of the transcendence in daily life (Underwood and Teresi, 2002). After qualitative study and repeated exploratory and confirmatory factor analysis on different populations, Underwood and Teresi (2002) developed the Daily Spiritual Experience Scale (DSES) which is a single factor, 16-item self-report scale. The items measure experience rather than particular beliefs or rituals, and intend to transcend religious and cultural boundaries. The scale has high internal consistency with Cronbach’s alpha at 0.95, as well as good construct validity. DSES has attracted researchers from different countries, including France, Spain, South Korea, and Vietnam (Underwood, 2006). Ng et al. (2009a) validated the Chinese DSES in Hong Kong Chinese population and revealed robust psychometric properties of the 16-item single factor structure.

#### Body-Mind-Spirit Well-Being Inventory (BMSWBI)

In response to the growing popularity of multidimensional BMS interventions and a corresponding need for a multidimensional outcome measure, Ng et al. (2005) developed BMSWBI, a self-report multi-item scale with 4 factors, namely Physical Distress, Positive and Negative Affect, Daily Functioning, and Spirituality. The scales have high reliability, with alpha coefficients ranging from 0.87 to 0.92. The tool has been used in a wide range of health studies, and the scale validation paper has been cited over 90 times in academic publications (Google Scholar, 2016).

#### Research Gap and Significance of the Proposed Study

At a practical level, community mental health workers of ICCMW are working under chronic stress and are vulnerable to burnout. However, they lack sufficient and continued emotional support. In light of the promising findings in the pilot trials, the brief daily BMS program may be an effective and feasible intervention for these social workers in mental health service to foster their emotional capacity and work engagement. In this regard, a more rigorous trial of the program is worth pursuing. If the eventual research results are positive, they know how of fostering sustainable emotional capacity and work engagement will be transferable to other emotionally demanding workplaces.

At a theoretical level, the study will reveal a new understanding of work engagement. Our pilot trials revealed a reduction of exceptional high engagement alongside with reduction in burnout. And previous studies also suggest the level of work engagement is not the higher the better and some negative consequences may be caused by over-engagement (Beckers et al., 2004; Beal et al., 2005; Bakker et al., 2011). Engagement may be like ‘fire’ fueling us at work, but it can ‘burn’ if it is overly strong. While most researches on work engagement focus on its positive consequences, studies on the “dark side” is inadequate (Crawford et al., 2010; Christian et al., 2011; Bailey et al., 2017). Therefore, this study will enrich the understanding of work engagement and is expected to find an optimal range for work engagement.

## Research Methods and Design

### Research Aim and Objectives

The overall aim of the proposed research is to pursue the further rigorous trial of the brief daily BMS program, which demonstrated good potentials in the pilot studies. The specific objectives are:

(1)To evaluate the efficacy of the brief daily BMS program in reducing burnout and enhancing engagement for community mental health workers;(2)To examine the trajectory of burnout, especially exhaustion, during a 3-month intervention and 3-month post-intervention periods; and(3)To examine the trajectory of engagement during a 3-month intervention and 3-month post-intervention periods.

### Study Design

A multi-site RCT design is adopted. All the 24 ICCMWs will be invited to join this research. Assuming a conservative response rate of 60–70%, about 14–17 ICCMWs will join. At each site, a pair of intervention (brief daily BMS group) and control groups (tea break group) will be run. Each group will have about 10 participants. Thus, there will be a totally about 280–340 participants randomly assigned to either an intervention or control group. The study will be registered with the Clinical Trials Centre of The University of Hong Kong.

### Hypotheses

In light of the literature and findings of the pilot trials, we have the following hypotheses:

H1: Reduction of burnout will be observed within the 3-month intervention period;H2: Rebound of burnout will be observed within the 3-month post-intervention period;H3: A narrowing of range in work engagement will be observed within the 3-month intervention period; andH4: A widening of range in work engagement will be observed within the 3-month post-intervention period.

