### Study Setting

This study will use a two-armed randomized-controlled trial design to compare the intervention group (BMS group) and control group (Tea break group). Researchers will promote the program in all 24 ICCMWs in Hong Kong and eligible participants will be recruited from the ICCMWs.

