To control for the social gathering effects of the experimental group, a control group in the format of daily 15-min tea break will be organized in parallel at the same site on every workday during the 3-month intervention period. A participant of the control group will be assigned as the coordinator who will take care of the basic logistics, such as room and materials booking, time keeping, and keeping an attendance record of participants. The tea-break is to be conducted in a quiet room provided with the usual drinks and snacks available for staff at the site. The tea-break is unstructured. During the 15 min, participants are free to enjoy the drinks and snacks, and interact with other group members. Similar to the intervention groups, each control group may decide on their preferred time slot on a day for the tea-break that fits their work schedule. The same set of questionnaires will be administered on participants of each control group by the research assistant of the project at baseline (T0), then at monthly intervals (T1–T6). Figure 1 CONSORT diagram depicts the flow of the trial.

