### Data Analysis

Both completers and intention-to-treat analysis will be performed. In the intention-to-treat analysis, missing data will be handled by ‘last observation carried forward.’ With a 2-arm RCT design, the efficacy of the intervention will be examined by repeated measures MANOVA on both primary and secondary outcome variables. Partial eta-squared (η^2^) values are computed to assess the effect sizes; values of 0.02, 0.13, and 0.26 suggest small, medium, and large effect sizes, respectively (Pierce et al., 2004). To investigate within group effects, serial trend analysis from T0 to T6 will be conducted on the outcome variables. In the case of work engagement, changes in a range of scores from T0 to T6 will also be examined. The associations between primary and secondary outcome variables will be explored by correlational and multiple regression analyses.

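### H1 to H4 name no comparator, and H3 and H4 have no between-arm test, so changes shared with the tea-break arm would satisfy them as worded

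*Protocol article*

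**What the plan says.** **Hypotheses.** H1 is "H1: Reduction of burnout will be observed within the 3-month intervention period" and H2 is "H2: Rebound of burnout will be observed within the 3-month post-intervention period". H3 is "H3: A narrowing of range in work engagement will be observed within the 3-month intervention period", and H4 is its mirror image after the intervention ends. Each describes a change over time. None names an arm, a comparator or a difference.

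**Whose change is meant.** In the abstract's discussion, "participants in the Brief Daily BMS intervention group are expected to have a reduced burnout level", and afterwards "a rebound of burnout level and a widening of range in work engagement are expected to be observed in the same group of participants". The Conclusion repeats this. Neither place compares with tea breaks.

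**Purpose of the design.** Under Study Setting: "This study will use a two-armed randomized-controlled trial design to compare the intervention group (BMS group) and control group (Tea break group"). Under Procedures, the tea-break arm is there "To control for the social gathering effects of the experimental group". It runs at the same site, daily, over the same three months.

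**Analysis.** The Data Analysis section names three relevant items:
- a repeated measures MANOVA to examine efficacy in the two-arm design;
- a trend analysis: "To investigate within group effects, serial trend analysis from T0 to T6 will be conducted on the outcome variables";
- for engagement, an examination of how the range of scores changes from T0 to T6, with no comparison of arms mentioned.

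No numbered hypothesis is linked to any of the three.

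**The concern.** A fall to T3 and a rise to T6 seen in the BMS arm mixes several things: any program effect, the effect of a daily 15-minute break with colleagues, regression to the mean in stressed volunteers, repeated questionnaires and calendar effects. The tea-break arm was added so that at least the social part could be subtracted, but the hypotheses do not ask for that subtraction.

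H2 is the most exposed of the burnout hypotheses. Both arms stop their daily gathering after three months, so if the break itself helps, burnout should rise again in both. H3 and H4 are the weakest on analysis, because nothing named in the plan compares the spread of engagement between arms. At stake is whether the trial can report its hypotheses as supported when the randomised arms do not differ.

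**Working it through.** **Step 1: each hypothesis against the named analyses.**
- H1 and H2: the MANOVA covers mean burnout in both arms over seven visits (T0 to T6). The article does not say which effect decides. A main effect of time from that model would fit H1 as worded; only a group-by-time effect compares the arms. Even an overall group-by-time test over seven visits does not separate T0-T3 from T3-T6, which is what distinguishes H1 from H2.
- H3 and H4: these concern range. A MANOVA compares mean vectors, and two arms can have equal means and different spreads. The one analysis named for range states no arm comparison.

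**Step 2: size of the problem for H1, by illustration.** The article gives no figure for a shared change or for the pre-post correlation, so both are assumed.
- The target is 224, or 112 per arm; with the stated 10% attrition, 112 × 0.9 = 100.8, about 101 analysed. (The Study Design section gives 280 to 340 in total; the 224 of the abstract and sample-size section is used here.)
- Suppose there is no program effect and both arms fall by d SD. The standardised paired change is d_z = d / √(2(1 − r)); with r = 0.5, d_z = d.
- Noncentrality is d_z√n, compared with t(0.975; 100) = 1.984. For d = 0.2: 0.2 × √101 = 2.01, power 0.512. For d = 0.3: 0.3 × √101 = 3.01, power 0.848.
- With r = 0.6 the two figures are 0.605 and 0.916.
- With 67 analysed (75 × 0.9 = 67.5) and r = 0.5 they are 0.364 and 0.677.
- A two-sided between-arm test is significant in 5% of such trials, and favours BMS in 2.5%.

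These are chances of a significant two-time-point paired change in one arm. They are not error rates of the planned MANOVA.

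**Step 3: the stated sample size, and what an arm contrast would need.** The sample-size section gives effect size 0.4, 90% power, significance level 0.05, 10% attrition and 75 per arm.
- Two-sample comparison, two-sided: n = 2(1.960 + 1.282)² / 0.4² = 131.4, so 132 completers per arm; 132 / 0.9 = 146.7, so 147 enrolled. The stated 75 is not reproduced.
- One-group paired test at d = 0.4: 67.6 completers; 67.6 / 0.9 = 75.1. This matches.
- Baseline-adjusted between-arm comparison with r = 0.7: 132 × (1 − 0.49) = 67.3; 67.3 / 0.9 = 74.8. This also matches, but needs a correlation the article does not state.

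Power of the unadjusted between-arm contrast at d = 0.4, no clustering: 75 enrolled (67.5 completers) gives 0.4 × √(67.5/2) = 2.32; 2.32 − 1.96 = 0.36, about 64%. With 112 enrolled (about 101 completers), 0.4 × √(101/2) = 2.84; 2.84 − 1.96 = 0.88, about 81%.

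**The case against.** The strongest reply is that the protocol already has a between-arm analysis. The MANOVA is assigned to efficacy in the two-arm design, it covers burnout and engagement as primary outcomes, and it would normally carry a group-by-time test. The trend analysis is labelled within-group and fits objectives 2 and 3, which concern trajectories. Choosing the model term that decides efficacy is detail an article may leave to an analysis plan.

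Much of this stands. A reader might infer that the within-group trend analysis decides H1 to H4, that a shared fall would be reported as proof of the program, or that the benefit of randomisation is discarded. The documents do not support those readings: no text assigns the trend analysis to the hypotheses, and for mean burnout and engagement a between-arm analysis is named. A reader might also infer from the match at 75 that the sample size came from a paired test. Step 3 shows another route to the same figure, so the match proves nothing about its derivation.

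The reply does not reach two things. The hypotheses are stated in this document, not left to another, and they omit the comparator that the design was built to supply. And no MANOVA of means can answer H3 and H4.

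**Conclusion.** The point holds in this form. As worded, H1 to H4 could all be met with identical arms, which conflicts with the comparative purpose stated under Study Setting and Procedures. The MANOVA reduces the risk for mean burnout and engagement but is not tied to H1 or H2 and does not isolate their time windows. For H3 and H4 no between-arm test is named.

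The size depends on assumptions. With a common fall of 0.2 to 0.3 SD, r = 0.5 and 101 analysed per arm, a BMS-only test would show a significant fall in about 51% to 85% of trials with no program effect. Those inputs are illustrative; the wording defect depends on none of them. The power figures assume individual-level analysis, with no clustering by group and no gain from covariates.

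**What to change.** 1. State H1 as BMS minus tea break in change in burnout from T0 to T3, and H2 as the same difference from T3 to T6. Test each as a pre-stated group-by-time contrast.
2. State H3 and H4 as between-arm comparisons of change in the spread of engagement over the same two windows. Name a test for dispersion, for example a variance ratio, or a Levene-type test with a bootstrap interval. Group-by-time contrasts in a model for means will not serve here.
3. Label the within-group trends from T0 to T6 as descriptive, and align the expectations in the abstract and conclusion with the reworded hypotheses.
4. Restate the power for the between-arm contrast, giving any baseline correlation relied on.

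Items 1 to 3 need rewording and a few analysis sentences, but no new data. The cost lies in item 4: without covariate gain, 90% power at d = 0.4 needs 147 enrolled per arm (294 in total) against the 224 targeted, so either the power claim falls to about 81% or a justified adjusted analysis must make up the difference. Clustering by group would lower these figures.
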